### Sample size required

The sample size required for a full-scale trial is based on a minimal clinical difference of 50 points on the primary outcome measure the IBS Symptom Severity Score [19]. A residual standard deviation of 90 points was observed in our pilot [18], and taking into account potential sampling bias [28] by using a one-sided 90% confidence interval for the variance, we estimate an adjusted standard deviation to be 105 points. Using this estimate, the sample size required to detect a difference at 90% power and 5% significance level is 188 patients in a two-arm trial. To allow for loss to follow up, of a similar proportion observed in the pilot, our proposed trial requires 220 patients.

For the nested qualitative study, we will collect data from 30 patients, a sample size that is likely to be sufficient to map the diversity of patients in primary care [29]. We will use purposive sampling guided by a matrix based on gender, intervention, preference, and baseline IBS severity as illustrated below in Table 1.

**Table 1 T1:** Qualitative sampling matrix

Baseline IBS Score	Preferred Acupuncture		Preferred Other		Total	
	Male	Female	Male	Female	Male	Female
**Mild - Moderate**	3-4	3-4	3-4	3-4	**6-8**	**6-8**
**Severe**	3-4	3-4	3-4	3-4	**6-8**	**6-8**
**Total**	**6-8**	**6-8**	**6-8**	**6-8**	**12-16**	**12-16**

We will also collect qualitative data from 10 GPs and 10 acupuncturists using convenience samples of practitioners in North Yorkshire, excluding those involved in the trial. It has been suggested that a sample size of 10 is adequate for phenomenological studies because researchers are seeking common features of experience [30].

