**Methods/Design:**

In this pragmatic randomised controlled trial we will randomise patients recruited directly from GP databases to either 10 sessions of acupuncture plus usual GP care or to usual GP care alone. The primary clinical outcome will be the IBS Symptom Severity Score (SSS) (maximum score 500) at three months, and at 12 month assessing whether there is an overall benefit. We estimate the sample size required to detect a minimum clinical difference at 90% power and 5% significance to be 188 patients. To allow for loss to follow up we will recruit 220 patients drawn from an estimated primary care population of 140 000. Analysis will be by intention-to-treat, and multiple imputation is to be used for missing data.

In a nested qualitative study using in-depth interviews, we will explore how patients, acupuncturists, and GPs explain and subsequently understand acupuncture to work. We will use purposive sampling to identify patients and flexible topic guides for the interviews. The data analysis will lead to a thematic description of how patients and practitioners explain how acupuncture works, and whether or not the explanations influence treatment outcome and/or referrals.

We will undertake a cost-effectiveness analysis at 12 months by comparing resource use in the two groups with any treatment benefit. We will use the EQ-5D to measure health-related quality of life and convert into quality adjusted life years (QALYs). We will generate cost effectiveness acceptability curves (CEACs) exploring the probability that acupuncture will produce an acceptable cost per QALY at different cost-effectiveness thresholds.

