### Participant recruitment criteria

To recruit participants, we will use the 'database' recruitment method as we did for the pilot [18]. Participants will be identified via the databases of GP practices in the NHS North Yorkshire & York Primary Care Trust. Our inclusion criteria are that participants must be aged 18 or older, with a diagnosis of IBS from their GP. We will exclude participants who do not speak English, who score less than 100 on the IBS Symptom Severity Score (SSS) [19], who have a current diagnosis of haemophilia, hepatitis, HIV, or cancer, who have had major gastrointestinal surgery in the previous six months, who are pregnant, who have a history of psychosis or substance abuse, or who are receiving acupuncture at the time. Participants will be assessed for IBS using the Rome III criteria [20]. In our pilot study, based in Birmingham, 32 eligible participants consented to participate from four GP practices that together had a registered list size of 20,300 [18]. For the proposed research, we estimate that 220 participants are needed (see below for sample size justification). To recruit this number, we will need a total primary care list size of approximately 140,000 patients, equivalent to 14 GP practices with an average of 10,000 patients each. We plan to recruit GP practices in geographically contained groups, such that each group of practices is located near a clinic that provides acupuncture from qualified acupuncturists. These groups are likely to be in the larger centres of population in the region. Based on our pilot, we estimate that recruitment will take 12 months.

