### Randomisation and blinding

We will randomise participants to receive either a short course of traditional acupuncture plus usual GP care or usual GP care alone, using simple concealed randomisation, the most robust method of avoiding possible selection bias [21]. The randomisation sequence will be computer generated at the University of York by an independent data manager at the York Trials Unit, and concealed from the researcher who will subsequently inform participants of their allocation. For those participants allocated to acupuncture, the selection of an acupuncture practitioner will be made by appointment availability and convenience for the participant. As this is a pragmatic trial, neither participants nor researchers will be blind to treatment allocation. Whilst randomisation eliminates selection bias, there are other sources of bias we need to avoid. To assess the impact of participant preferences, we propose to ask participants at baseline for their treatment preferences [22]. To avoid bias due to attrition, participants in both groups will be followed up carefully. Participants will also be given £5 as an incentive to complete the final follow-up questionnaire (they will receive the incentive whether or not they actually complete the forms) in order to reduce attrition rates. Incentives such as this have been shown to improve follow-up rates [23].

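### The adjusted SD of 105 is presented as a one-sided 90% limit, but with a pilot of at most 32 patients the exact limit is about 108 to 111

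*Protocol article*

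**What the plan says.** The section "Sample size required" in the protocol article builds the sample size in four steps.

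- The target difference on the IBS Symptom Severity Score: the calculation is "based on a minimal clinical difference of 50 points on the primary outcome measure".
- The variability: "A residual standard deviation of 90 points was observed in our pilot".
- An allowance for sampling error in that pilot SD: "by using a one-sided 90% confidence interval for the variance, we estimate an adjusted standard deviation to be 105 points".
- The result: "the sample size required to detect a difference at 90% power and 5% significance level is 188 patients in a two-arm trial", raised to 220 for loss to follow-up at a rate said to resemble the pilot's.

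The abstract repeats the result: "We estimate the sample size required to detect a minimum clinical difference at 90% power and 5% significance to be 188 patients". The size of the pilot is given under "Participant recruitment criteria": "32 eligible participants consented to participate from four GP practices". The Discussion reports that 233 patients were recruited. The article states neither the residual degrees of freedom behind the SD of 90 nor the formula used for the limit.

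**The concern.** An upper confidence limit for a variance depends on the point estimate, the confidence level and the degrees of freedom. The article gives the first two and caps the third through the pilot's size. With so small a pilot, a one-sided 90% limit should lie further above 90 than 105 does.

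The inflation step is there to guard against a pilot SD that came out too low by chance. If 105 is not a 90% limit, that guard is weaker than stated, and the power at the SD the method was meant to deliver is somewhat below 90%.

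**Working it through.** **Inputs.** Difference 50, pilot residual SD 90, adjusted SD 105, 90% power, 5% significance, 188 analysed and 220 recruited, all from "Sample size required"; 32 pilot patients from "Participant recruitment criteria"; 233 recruited from the Discussion. Assumed: two-sided test, 1:1 allocation, and a pilot residual SD based on one outcome per patient.

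**Step 1: from SD 105 to 188.** The normal formula gives 2 × (1.960 + 1.2816)² × 105² / 50² = 92.7, so 93 per arm. The two-sample t-test (noncentral t) needs 94 per arm, or 188 in total, with power 90.1%. The plan's figure is reproduced, which also supports the two-sided and 1:1 assumptions.

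**Step 2: range of pilot degrees of freedom.** The ceiling is 32 − 1 = 31 (no losses, only a mean fitted). Fitting intercept, arm and baseline to all 32 leaves 29. The retention implied by the plan is 188/220 = 0.8545, a loss of 14.5%. Applied to the pilot, 32 × 0.8545 is about 27 completers, leaving 27 − 3 = 24. The range used is therefore 24 to 31.

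**Step 3: exact one-sided 90% upper limit.** The formula is 90 × √(df / χ²), where χ² is the lower 10% point of the chi-square distribution on df degrees of freedom. The last column is the confidence level that 105 actually carries, P(χ² > df × (90/105)²).

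| df | χ² 10% point | Limit for SD | Actual level of 105 |
|---|---|---|---|
| 24 | 15.66 | 111.4 | 82.0% |
| 29 | 19.77 | 109.0 | 84.8% |
| 31 | 21.43 | 108.2 | 85.7% |
| 42 | 30.77 | 105.2 | 89.8% |
| 43 | 31.63 | 104.9 | 90.1% |

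So 105 corresponds to about 42 to 43 degrees of freedom. Rounding of the 90 does not close the gap: a pilot SD of 89.5 with 31 degrees of freedom still gives 107.6.

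**Step 4: can another formula give 105?** Yes, a large-sample normal approximation can.

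- On the variance, 90 × √(1 + 1.2816 × √(2/df)) gives 105.3 at df 24 and 105.1 at df 25.
- On the SD, 90 × (1 + 1.2816/√(2 df)) gives 105.1 at df 29 and 104.9 at df 30.

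**Step 5: consequence (two-sample t-test, difference 50).** Recruited numbers divide the analysed number by 0.8545. The 233 recruited correspond to 233 × 0.8545 = about 199 analysed.

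| SD used | Analysed for 90% power | Recruited | Power, 188 analysed | Power, about 199 analysed |
|---|---|---|---|---|
| 105 (plan) | 188 | 220 | 90.1% | – |
| 108.2 (df 31) | 200 | 235 | 88.3% | 90.0% |
| 109.0 (df 29) | 202 | 237 | 87.9% | 89.6% |
| 111.4 (df 24) | 212 | 249 | 86.4% | 88.3% |

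At the pilot's observed SD of 90, 188 analysed give 96.6% power.

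**The case against.** The strongest reply is that the article names no formula and no degrees of freedom, and that a normal approximation to the same limit gives 105 at values a 32-patient pilot could supply. That stands as a plausible account of where 105 came from, so it cannot be called unobtainable. It does not rescue the label: at 24 to 31 degrees of freedom 105 carries about 82 to 86% confidence, whichever formula produced it.

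A second reply is that the pilot report and the reference cited for the adjustment are not at hand, and that a residual SD pooled over several follow-up times would have different degrees of freedom. This also stands as a caveat. The range of 24 to 31 is an assumption tied to one outcome per patient. A condensed article may leave such details to the full protocol, so their absence is not itself the point.

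A reader might go further and infer that 188 patients do not give 90% power, or that the trial is underpowered. The article does not support that. It claims 90% power at SD 105, and at that SD the claim is correct, in the abstract as well. The planning value remains cautious relative to the observed 90, and actual power depends on the true SD, which the documents cannot settle.

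**Conclusion.** The point holds for the inflation step only. With at most 32 pilot patients and one outcome each (24 to 31 degrees of freedom assumed), the exact one-sided 90% limit is about 108 to 111. The stated 105 is about an 82 to 86% limit.

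The effect is modest. If the true SD equalled the exact limit, power with 188 analysed would fall about 2 to 4 percentage points below 90%, and the analysed number would be 12 to 24 short of the 200 to 212 needed. Recruitment of 233 recovers most of this. The figure still merits correction, because the stated sample size rests on it and anyone can check it. These results assume a two-sided test, 1:1 allocation and the plan's implied 14.5% loss.

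**What to change.** Either of two rewordings settles it, with no change to enrolment.

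1. Recompute the limit by the exact chi-square formula with the pilot's actual residual degrees of freedom, and state both. Then give the adjusted SD (about 108 to 111 on the range assumed here) and the power at that SD for 188 analysed and for the number recruited. The authors should use their own degrees of freedom, not the assumed range.
2. Keep 105 and 188, describe 105 as roughly an 82 to 86% upper limit (or as a normal approximation, if that was used), and say that the 90% power is conditional on an SD of 105.

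The cost is an edit to the sample size paragraph and the matching sentence in the abstract, and a slightly less favourable stated figure.

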### Data analysis

We will use intention to treat analysis; all participants will be included in their randomised groups, whether or not they have received their allocated treatment. The primary outcome will be the IBS SSS at three months, using analysis of covariance while adjusting for baseline scores and GP practice, and at 12 months, using multi-level modelling with IBS SSS scores at 3 month intervals. Sensitivity to missing outcomes data will be addressed using multiple imputation. We will also compare between groups the secondary outcomes of IBS non-colonic symptom scores, quality of life (SF-12) and anxiety and depression (HADS). As a secondary analysis, we will explore the interaction between the effect of acupuncture and variables assessed prior to randomisation: participants' belief in acupuncture, expectations that acupuncture will help their IBS (expectation), patient treatment preference and whether patients received their preferred treatment or not. Further secondary analyses will investigate the effects of variation in outcome between acupuncturists.

For the qualitative data, we will transcribe the interviews, identify recurring themes and develop a conceptual framework to apply to the complete data set. Data analysis will be conducted by two researchers working independently to ensure a thorough analysis. Synthesised data will provide a thematic description of how patients and practitioners understand and explain acupuncture to work, and whether or not this explanation influences treatment outcome and/or referrals.

### Cost effectiveness

We will undertake a cost-effectiveness analysis at 12 months by comparing resource use in the two groups with any treatment benefit in an incremental cost-effectiveness ratio. The primary analysis will calculate cost-effectiveness from an NHS perspective because of the potential to influence health policy. However, we will also perform cost-effectiveness calculations from a societal perspective to ensure that this research will not be limited in its usefulness. We will collect data from patients and GPs about patients' resource use, such as visits to their GP, visits to other health providers, both within and outside the NHS and medication use, as well as measuring their days off and whether usual activities are affected by their IBS. We will use EQ-5D to measure health-related quality of life and convert into quality adjusted life years (QALYs), in order to calculate an incremental cost effectiveness ratio (cost per QALY gained), after adjusting for baseline EQ-5D score [31]. To measure presenteeism and absenteeism, we will use the Work Productivity and Activity Impairment instrument (WPAI) and convert the scores into a monetary value [32]. We will also use a net monetary benefit approach to generate cost effectiveness acceptability curves (CEACs) exploring the probability that acupuncture will produce an acceptable cost per QALY at different cost-effectiveness thresholds. This approach accounts directly for uncertainty around the estimates of costs and effects, which is particularly important as this trial is powered on the basis of the clinical effectiveness measure (IBS SSS) rather than the economic outcome measure (EQ-5D). If the intervention is found to be not cost-effective at 12 months, then evaluation over a longer time frame may be considered.

## Discussion

The proposed research received ethics approval from the York Research Ethics Committee (08/H1311/66). The trial recruited 233 patients between November 2008 and June 2009. Written informed consent has been obtained from all participants. Published results are expected in 2011.

## Abbreviations

EQ-5D: EuroQol health utility measure; IBS: irritable bowel syndrome; SSS: Symptom Severity Score; WPAI: Work Productivity and Activity Impairment Instrument
